#### Intervention (2D Educational Video)

Participants will watch an educational video that effectively summarizes the causes and symptoms of moral distress and injury and the potential interventions at the individual, team, and organizational levels.

#### Posttest: Virtual Reality Scenario

For the posttest, the virtual reality scenario with moral distress and injury knowledge and its respective interventions are repeated.

#### Debrief

After completing the pre- and posttest, participants will engage in a debrief led by the researchers. The debrief includes open-ended questions that will encourage the participants to speak about their experience in the virtual reality setting, followed by an exit survey. If needed, participants will be able to speak with a psychotherapist at the Center for Depression and Suicide Studies at St. Michael’s Hospital.

#### Longitudinal Monitoring

After completing the session, participants will use the app for longitudinal monitoring by collecting passive and active data to understand the distress experienced in real-time.

### Compound Intervention

The compound intervention is composed of the virtual reality simulation-based educational intervention and data collection of mental health and moral injury surveys. The virtual reality simulation-based educational intervention contains a moral injury educational video based on the Moral Injury Guide developed by the Ottawa PTSD Center for Excellence [17].

The latter component of the compound intervention evaluates the effectiveness of the virtual reality simulation-based educational intervention through mental health surveys. These surveys include the Perceived Stress Scale (PSS), Moral Injury Outcome Scale (MIOS), Igroup presence questionnaire (IPQ), and Adapted Moral Injury Symptom Scale: Health care Professionals Version (MISS-HP). PSS is a self-report instrument that evaluates level of stress. MIOS and MISS-HP are tools that evaluate the effect of moral injury, and the IPQ is a questionnaire that evaluates the experience of presence during virtual reality simulations. We will use this information to improve our compounded intervention for use on digital platforms iteratively.

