**Methods:**

This will be a prospective, single cohort, pre- and posttest study examining the effect of a brief informative video describing moral distress on perceptual, psychological, and physiological indicators of stress and decision-making during a scenario known to potentially elicit moral distress. To accomplish this, we have developed a virtual reality simulation that will be used before and after the digital intervention for monitoring short-term impacts. The simulation involves an intensive care unit setting during the COVID-19 pandemic, and participants will be placed in morally challenging situations. The participants will be engaged in an educational intervention at the individual, team, and organizational levels. During each test, data will be collected for (1) physiological measures of stress and after each test, data will be collected regarding (2) thoughts, feelings and behaviors during a morally challenging situation, and (3) perceptual estimates of psychological stress. In addition, participants will continue to be monitored for moral distress and other psychological stresses for 8 weeks through our Digital intervention/intelligence Group mobile platform. Finally, a comparison will be conducted using machine learning and biostatistical techniques to analyze the short- and long-term impacts of the virtual reality intervention.

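### The intervention is named inconsistently (the video, a VR intervention containing it, or a compound including the surveys), and a posttest-minus-pretest change cannot be reported as the impact of the VR intervention

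*Protocol article*

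**What the plan says.** The article describes the intervention in three ways.

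- **The video.** The Abstract (Methods) describes a single-cohort pre/post study "examining the effect of a brief informative video describing moral distress on perceptual, psychological, and physiological indicators of stress". VR has the role of a test there: "we have developed a virtual reality simulation that will be used before and after the digital intervention for monitoring short-term impacts". The Methods subsection whose heading contains the word Intervention describes only the 2D video, and the Overview treats the VR runs as the pretest and posttest.
- **VR containing the video.** The same Abstract paragraph closes with a plan to "analyze the short- and long-term impacts of the virtual reality intervention". The Compound Intervention section states: "The virtual reality simulation-based educational intervention contains a moral injury educational video".
- **VR, video and surveys.** The Compound Intervention section also says: "The compound intervention is composed of the virtual reality simulation-based educational intervention and data collection of mental health and moral injury surveys". It then gives the survey part its task: "The latter component of the compound intervention evaluates the effectiveness of the virtual reality simulation-based educational intervention through mental health surveys". The surveys are the PSS, MIOS, IPQ and MISS-HP.

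Two further sections blur the line between test and treatment. The pretest section says the pretest scenario will at first contain all the suggested individual-, team- and organizational-level interventions and will examine their efficacy. The posttest section says the scenario is repeated together with its interventions.

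**The concern.** In a single uncontrolled cohort, an effect is defined entirely by what is compared with what. If the video is the intervention, the natural *before* is the measurement at the first VR run. If VR belongs to the intervention, the *before* has to precede that run. The article does not tie either comparison to a name.

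As written, the change between the two VR runs could be published as the impact of the VR intervention, although both measurements follow VR exposure. The article says that a demonstration of feasibility will lead to later efficacy studies. Those studies need to know which intervention was shown to be feasible and what the observed change represents.

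**Working it through.** The article states no effect size, standard deviation or power for this comparison, so there is no figure to reproduce. The check is to set out what each available contrast contains.

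**Time points**
- T0: before any VR. Trial Design mentions presurvey data at the prebrief.
- T1: at the pretest VR run.
- T2: at the posttest VR run, after the video.
- T3: at the end of the 8 weeks of app monitoring.

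**Components of change** (symbols only; the article gives no values)
- s: change evoked by the first VR run. The Abstract says the scenario is known to be capable of eliciting moral distress.
- h: effect of going through the same scenario a second time, such as habituation or renewed distress.
- v: effect of the video.
- m: everything after the session, including app use. The app offers health tips and sends alerts with recommendations (Mobile Platform; Passive Data; Table 4).

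**Contrasts**
1. T2 − T1 = h + v. The term s cancels because the first VR run is in both measurements. What remains is the video plus the repeat run.
2. T2 − T0 = s + h + v. This is the whole session: two VR runs plus the video.
3. T3 − T0 = s + h + v + m, where s, h and v now stand for whatever persists at 8 weeks. This is the session plus app use and anything else that happened in that period.

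Contrasts 1 and 2 differ by s. If s = 0 they agree. If s is positive (more distress) and h + v is negative (less distress), they have opposite signs when s > −(h + v). Nothing in the article says whether that condition would be met.

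**Which name fits which contrast**
- *Video*: contrast 1 is the nearest, but h cannot be separated from v without a group that repeats the scenario without the video.
- *VR intervention*: contrast 1 does not fit because s has cancelled. Contrast 2 includes VR but mixes it with the video.
- *Compound including surveys*: everyone is surveyed, so no contrast shows what the surveying contributes.

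**Does one scale cover T0, T1 and T2?** Subjective Data Collection puts the MIOS and PSS at the beginning and end of the study and calls the MISS-HP a local assessment of distress. It otherwise says only that the scales are answered throughout the experiment. Trial Design does not name the presurvey scales, and the figure showing the experiment components is not reproduced in the text at hand. A common scale at all three points is therefore not confirmed.

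**The case against.** The best defence is that the order of events is clear: VR pretest, video, VR posttest. The video is shown on the headset, so *virtual reality intervention* can be read as shorthand for the session. The study is a feasibility pilot that leaves efficacy to later work, and the analyses it describes are mainly feature extraction and classification, with no effect estimate fixed. Article length may explain missing detail.

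Much of this stands. The sequence is clear, and the consequences are limited by the pilot's aims. But the article also says it examines an effect, analyses impacts and evaluates effectiveness, and condensing a fuller document does not explain statements that conflict with each other.

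Two stronger readings are tempting and are not supported:

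- *The estimate changes sign with the definition.* This needs one scale at all three time points and a rise at the first run larger than the later fall. The article confirms neither. If only the two VR runs are compared, the number is the same under every name and only its meaning changes.
- *Because the surveys are part of the intervention, no baseline exists.* The Compound Intervention section says the surveys evaluate the other component, the VR-based educational intervention, and not themselves. The first survey can serve as baseline for that component. The fault is that measurement is grouped under treatment.

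**Conclusion.** The inconsistency is real and stands in the current text. With VR already in the pretest and no control, posttest minus pretest measures the change across the video and the repeat run, and it cannot be reported as the impact of the VR intervention. This follows from the design at any sample size.

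A contrast from a pre-VR baseline would also contain whatever distress the first run evokes, and it could differ in size or direction from the pretest-to-posttest change. No magnitude can be given. The article supplies no values, and such a contrast assumes a common scale that it does not confirm. This is a correction worth making because it changes what the trial can conclude. It does not show that the design is unsuitable for a feasibility aim.

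**What to change.** 1. Name one intervention and use it consistently in the Abstract, the pretest, video and posttest sections, and Compound Intervention. The video as intervention with VR as the test setting fits the design in the Abstract.
2. List the PSS, MIOS, IPQ and MISS-HP as measures and take them out of the compound intervention.
3. Reconcile the pretest and posttest wording that places suggested interventions inside the scenario with the role chosen for VR.
4. Replace the phrase about impacts of the VR intervention with labelled contrasts:
   - posttest minus pretest: change across the video and the repeat run;
   - presurvey to session end, where the same scale is used: change after the whole session (two VR runs plus video);
   - 8-week change: change after the session plus app use, including its alerts and recommendations.
5. State that none of these isolates an effect of VR.

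The cost is wording in those sections, with no new data. The downside is that the result can no longer be described as the impact of the VR intervention.

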### Trial Design

This is a multilayer feasibility trial (Figure 2). The in-person session (Figure 3), begins with participant arrival at St. Michael’s Hospital Simulation Centre. This is followed by experimental set-up and prebrief. The prebrief is held to inform the participant of the purpose of the session, to collect presurvey data, and obtain written consent. The experimental set-up involves the attachment of the virtual reality equipment and physiological sensors. The debrief is hosted after the experiment and is composed of a semistructured interview, open-ended questions, and an exit survey. The purpose of the debrief is to obtain qualitative feedback on the session to better understand the participant experience.

The virtual reality session will be used for short-term monitoring of participants for acute distress. After the intervention, participants will use a mobile app (developed by the Digital intervention/intelligence Group) for long-term distress monitoring.

**Figure 2 figure2:**

Overview of the virtual reality experimental set-up and data collection.

**Figure 3 figure3:**
[figure not shown]
Diagram of experiment components. VR: virtual reality. MI: moral injury. IPQ: igroup presence questionnaire. MISS-HP: moral injury symptom scale: healthcare professionals version.

### Security and Privacy of the Study Data

During the session hosted at St. Michael’s Hospital Simulation Centre, data (CSV files, text files, audio, and video files from the session) will be securely uploaded to a password-protected drive. Only specific members of the project have access to the data. Responses on paper questionnaires will be input to a spreadsheet and stored on the encrypted drive. During the longitudinal monitoring part of the study, all active and passive data will be stored on the participant’s phone (if storage space is available) until those data are synced back to the back-end server. Data are transferred over a TLS layer; hence, it is encrypted by RSA Asymmetric Encryption Algorithm.

Study data will be stored for 10 years. No personal information will be collected through the mobile component of the study. Demographic data (ie, age, sex, type of job at Unity Health Toronto, diagnosis, and COVID-19 status) will be collected separately from data collected by the app. A study participant ID will link these data for final analysis.

The server and the dashboard will be hosted on the same virtual machine server, and the database will be hosted on a different database server (Multimedia Appendix 1).

### Virtual Reality Development

The first stage of the development involved defining the context of the scenario, with the support of a subject-matter expert, and determining how it connects to the domains *betrayal of the team*, *transgression of moral values*, *emotional response*, and *support and reframing in relation to guilt and loss of trust in colleagues and shame*.

An overview of the scenario was then outlined, describing the location, main characters, key points (eg, the removal of the ventilator), and the actions and reactions of each character. Based on this document, 2 activities were performed in parallel: the definition of the scenario script with the lines and actions of all characters and the development of the 3D assets (characters, objects, and environment) of the virtual reality scenario. Both activities were developed iteratively, with discussions and demonstrations during weekly meetings. The final version of the script includes 7 nonplayable characters (Table 1) and 4 conversations (Table 2), not including the initial tutorial.

For the virtual environment (Figure 4 and Figure 5), royalty-free models and scenarios were purchased and used as a starting point. They were combined and modified to fit the project's needs. Subject-matter experts provided feedback on key elements to make the environment appear closer to the reality of a Canadian hospital environment. The goal was to represent a standard intensive care unit with individual rooms for patients and a nursing station.

**Table 1 table1:** List of nonplayable characters.

Character	Description
Administrator	Intensive care unit team lead
Nurse	Intensive care unit nurse
[name]	[name], a 65-year-old man who has multiple comorbidities with COVID on a ventilator
[name] partner	Distraught, accusing the participant of cruelty, mismanagement, and malpractice
[name]	A 56-year-old woman has a more favorable prognosis
Medical Doctor 2	Another intensive care unit physician, not aware of the situation
Medical Doctor X	Highly experienced and respected intensivist whose advice and counsel are often sought

**Table 2 table2:** List of conversations.

Scene	Nonplayable characters	Description
Intensive care unit hallway	Administrator, nurse	Conversation between the participant, administrator, and nurse about the lack of ventilators. It is decided to move the ventilator from [name] to [name].
[name] room	[name], [name] partner	The participant must inform [name] partner about the decision to remove the ventilator.
Intensive care unit hallway 2	Medical doctor 2	A medical doctor questions the participant about what happened, and they witness [name] (now without the ventilator) going into cardiac arrest
Nursing station	Medical doctor X	An experienced medical doctor reaches out to the participant to provide counsel and provide support.

**Figure 4 figure4:**
[figure not shown]
Patient’s room with a patient connected to a ventilator.

**Figure 5 figure5:**
[figure not shown]
Nursing station, monitor station, and intensive care unit corridor.

To represent the nonplayable characters and the participant, royalty-free models were purchased as starting points. Based on these models, a customizable character system was implemented that allowed us to quickly modify external elements (such as clothing or masks) or the character’s characteristics, such as height and weight (Figure 6).

For the user interface, 2 semitranslucent panels are displayed as spatial elements in the virtual reality environment (Figure 7). The dialogue panel shows current nonplayable character’s photograph, name, and the text version of the dialogue being spoken. The interaction panel displays available choices (for example, the option *Continue* to advance to the following dialogue or a list of choices).

To interact with the panel, participants need to move one of the controllers, point to the desired choice, and click any buttons under the index finger or thumb. The participant can see a blue ray being casted from their index finger tip within the virtual reality environment, which turns yellow when hovering over the interactive panel (Figure 7). As additional visual feedback, dialogue choices include a highlight effect when the ray hovers over each.

**Figure 6 figure6:**
[figure not shown]
Testing 2 characters with different clothing and body parameters.

**Figure 7 figure7:**
[figure not shown]
User interface displaying the dialog and interaction panels, and the interaction ray from the right-hand index finger.

### Software and Hardware

The virtual reality scenarios were created using a cross-platform game engine (Unity 3D, Unity Technologies) that has been adopted, not only by the game industry, but also by film, architecture, and education industries [18]. The virtual reality scenario is played using a consumer-grade head-mounted display (Oculus Quest 2, MetaQuest) (Figure 8) that can track the user’s head movements with 6 degrees of freedom and track the user’s movements either in stationary mode (sitting in a chair) or in room mode (recommended room size is up to 2 m × 2 m), allowing the user to physically walk around within the defined boundaries. In addition, the system includes 2 handheld motion-tracked controllers that allow the user to interact with the environment and with virtual reality interface components. Our virtual reality scenarios will adopt stationary-mode tracking and use the handheld motion-tracked controllers for more accurate tracking.

**Figure 8 figure8:**
[figure not shown]
Oculus Quest 2 components.

Currently, Oculus Quest and Oculus Quest 2 are not Health Insurance Portability and Accountability Act–compliant. However, no data will be stored in the virtual reality device, and the Oculus framework is not used to develop our virtual reality app. The Oculus Quest 2 is connected to a virtual reality-capable PC laptop using a USB-C cable.

### Subjective Data Collection

We plan to collect subjective data such as qualitative data from surveys and open-ended feedback. As mentioned in the previous sections, the MISS-HP, IPQ, PSS, and MIOS will be answered throughout the experiment. At the end of the virtual reality session, an exit survey composed of open-ended and 3 multiple choice questions for general feedback.

Overall, the MIOS and PSS are evaluated at the beginning and end of the study for a global assessment of distress (Multimedia Appendix 2), whereas the MISS-HP is collected for a local assessment of distress (Multimedia Appendix 3).

### Objective Data Collection

During the virtual reality session, electrocardiogram, electrodermal activity, photoplethysmography, and respiration impedance sensors will be attached to the participant (Figure 9), and these data will be collected with an acquisition and analysis system (MP160, Biopac).

**Figure 9 figure9:**
[figure not shown]
Example of the physical set-up: researcher wearing the head-mounted display, controllers, and Biopac sensors during the virtual reality simulation.

### Virtual Reality Data Analysis

We will create a personalized digital phenotype profile, an objective parameter which will help track individual trends over time which will assist in identifying the efficacy of digital interventions and exposure to immersive virtual reality environments, for each participant using primarily heart rate, respiratory rate, oxygen saturation, and skin conductance (BioNomadix, Biopac) (Table 3). These signal features will be paired with reported psychological measures (scales) for a holistic understanding. Both cardiovascular and cerebrovascular dynamics can be captured with these data by deriving features such as heart rate, respiratory rate, and heart rate variability (which is related to the autonomic nervous system and affect states [19]). The autonomic nervous system is the control system that acts largely unconsciously and regulates bodily functions, including heart rate and respiratory rate. This system is the primary mechanism in control of the fight-or-flight response [19]. We expect that participants in stressful situations will have specific personalized digital phenotype profiles.

**Table 3 table3:** Description of sensors used and physiological signals collected.

Sensor	Description
Galvanic skin response (electrodermal activity)	Galvanic skin response, also known as electrodermal activity, is a sensor that collects the change in the sweat glands. It measures the electrical conduction of the skin. This sensor is commonly reflective of emotional state and arousal such as anxiety
Electrocardiogram	Electrocardiogram is a physiological signal electrocardiogram collects the electrical activity of the heart. We will measure the heart rate using electrocardiogram features that can be extracted can include heart rate variability and R-R intervals
Respiratory impedance	respiration impedance is a physiological signal that collects the respiration of a participant. It can be defined as the mechanical load of the respiratory system to ventilation. We will collect the number of breaths a participant takes
Photoplethysmography	A noninvasive sensor that uses a pulse oximeter to illuminate a light on the skin. By doing so, it measures the blood volume changes respiratory impedance

### Mobile Platform

#### Customized Digital intervention/intelligence Group Platform

We will use the app, which is based on an open-source mobile-based platform, LAMP (Learn, Assess, Manage, Prevent [20,21]), which is fully compliant with patient and participant confidentiality standards and is currently in use at various US, Canadian, and international hospitals [20]. Applicable privacy legislation include the Personal Health Information Protection Act of Ontario and The Personal Information Protection and Electronic Documents Act.

Learn: This module offers health tips and accurate health news from sources the participant can trust [20].

Assess: This module infers the participant’s mood and cognitive status (eg, depression, anxiety, etc) by asking the participant to complete surveys. In addition, this module collects the participant’s phone data (eg, geolocation, phone usage).

Manage: In this module, participants can maintain a journal by writing in a diary or have personalized interventions. However, only the participant can write or read the material in this module since all data collected here is personal and available only to the participant.

Prevent: This module uses a dashboard to post figures and curves summarizing the participant’s mood, cognitive status, and phone data, such as how fast the participant is moving.

The app is compatible with both iOS and Android platforms. It will be available for free download and for use by approved participants (log-in information will be provided after obtaining informed consent), and deidentified data will be stored at Unity Health Toronto. Furthermore, the platform will be tailored to collect information pertinent to the COVID-19 context. The platform collects various forms of active data (while the participant is using the app) and passive data (whether or not the user is actively using the app) [20]. Study participants will have the option of full access to their active and passive data in real time on the phone or web-based dashboard.

